## Abstract

**Background:**

Hypoglossal neuropathy is the most common lower cranial neuropathy detected as a delayed sequelae of Human Papillomavirus (HPV) -driven oropharyngeal cancer (OPC). Needle electromyography (EMG) is the gold standard for electrodiagnostic testing, but it is invasive and relies on subjective interpretation of the EMG signal. This study explores the potential of non-invasive high-density surface electromyography (_HDS_EMG) to detect and quantify hypoglossal neuropathy in OPC survivors.

**Objective:**

In an exploratory study, examine the feasibility of _HDS_EMG for rapid, non-invasive screening of hypoglossal nerve (CN XII) function and estimate the prevalence of hypoglossal neuropathy before and after oropharyngeal radiotherapy, and associate with patient-reported and clinician-graded functional outcomes. Machine learning performance will be measured through sensitivity, specificity, and F1 score, with a target area under the curve > 0.7 based on literature-reported EMG sensitivity and specificity.

**Methods:**

This protocol will recruit patients aged ≥ 18 years who receive radiation therapy for OPC at MD Anderson Cancer Center (MDACC) between 2024–2025 and consent to experimental _HDS_EMG testing. [name] Research Lab (The University of Utah, Salt Lake City, UT) will perform data analysis. Clinical data—including electrical impedance measurement (EIM), patient-reported outcomes, dysphagia grading, tongue functions, fibrosis grading, and needle EMG—will be collected from n = 36 patients. Features extracted from _HDS_EMG will be correlated with other clinical outcomes and used to train a machine learning classifier to quantify the severity of hypoglossal neuropathy.

## Introduction

Oropharyngeal squamous cell carcinoma, arising from the base of the tongue and tonsil, is increasing in incidence. We now recognize that many tumors are related to the human papillomavirus (HPV), and this trend is expected to continue without decline until at least 2045, despite current vaccination rates [1–4]. Patients with HPV-attributable oropharyngeal cancer (HPV-OPC) tend to have a more favorable survival prognosis than patients with a history of tobacco use [5].

Furthermore, hundreds of thousands of young survivors of HPV-OPC will live a significant portion of their lives with post-treatment toxicities from radiotherapy [1]. Normal tissue injury from radiotherapy along the hypoglossal nerve (cranial nerve XII), such as radiation-induced fibrosis or lymphedema, causes denervation of the tongue musculature, contributing to swallowing dysfunction and increasing the risk of choking and aspiration pneumonia (airway entry of liquids or food) [6–8]. These symptoms significantly decrease survivors’ quality of life (QOL) and, in the worst case, lead to tracheostomy or feeding tube insertion.

Clinicians identify and assess manifestations of hypoglossal neuropathy using patient-reported outcomes (PRO) questionnaires (e.g., MD Anderson Dysphagia Inventory [MDADI]; MD Anderson Symptom Inventory-Head and Neck [MDASI-HN]) and interviews regarding patient functional status (e.g., Performance Status Scale-Head and Neck Cancer [PSS-HN]). Cross-sectional cohort studies have used these indices to evaluate symptom burden in OPC survivors with and without hypoglossal neuropathy [5,6,9]. These studies found that patients with hypoglossal neuropathy scored 1.54 points worse on the MDASI-HN overall, with the most significant implications on bulbar symptoms, including difficulty with swallowing/chewing, choking, speech/voice, mucus, and fatigue [5]. Furthermore, MDADI, PSS-HN, and PRO scores showed that patients with cranial neuropathy experienced adverse functional status metrics like dietary restrictions, nutritional impairment, and a decline in public food consumption [6]. In that body of studies, the investigators demonstrated substantial risk and burden of lower cranial neuropathy (most commonly CN XII neuropathy) in OPC. However, these insights are subject to limitations of clinical surveillance metrics. The bias inherent in rudimentary clinical detection methods matched to PRO surveys and related measures increases the uncertainty of the conclusions, and symptom reports cannot be expected to mimic physiology or reveal the underlying mechanisms contributing to pathological states.

Current technologies constrain physiological measurement of the tongue. Tongue strength, as manometrically measured by the Iowa Oral Pressure Instrument (IOPI), is shown via meta-analysis as a valid tool for measuring tongue pressure and monitoring tongue treatment progression [10]. Hypoglossal nerve health can be assessed quantitatively using needle electromyography (EMG) of the genioglossus [11]. Experienced neurologists detect neuropathy by grading electromyograms on a numeric grading system from 0 (normal) to 4 (spontaneous fibrillation potentials filling the screen) [12,13]. Despite its clear value, needle EMG is invasive, can be performed only by trained specialists, and uses a coarse, subjective clinical grading scale. Action potentials are graded by the prevalence of specific patterns, as determined through visual or auditory analysis. Fibrillation potentials repeat in a definable, regular pattern, typically with a linear increase in the interspike interval. Voluntary MUPs fire in a semi-rhythmic pattern, with interspike interval changes of less than 10% [14].

We propose to investigate tongue high-density surface electromyography (_HDS_EMG) as a non-invasive alternative to needle EMG, motivated by previous work measuring electrical impedance myography with surface electrodes [15–17]. In the published literature, subcranial multichannel _HDS_EMG of the swallowing mechanism has a non-inferior signal-to-noise ratio (SNR) compared to larger gel electrodes [18,19]. Several robust decomposition algorithms exist for selectively reconstructing individual motor unit potentials (MUPs) from the surface [20]. We expect that signal abnormalities indicative of tongue neuropathy will manifest in processed _HDS_EMG signals, as they do in needle EMG, and will correlate with tongue function abnormalities revealed by functional outcomes examination. We propose that a machine-learning approach to _HDS_EMG will reveal the underlying relationship between tongue EMG waveform morphology and the presence of XII neuropathy, allowing for neuropathy grading on a continuous scale. We expect that revealed relationships may enable the early discovery of hypoglossal neuropathy, allowing clinicians to intervene before irreversible progression manifests.

## Materials and methods

### Study design

We propose an exploratory cross-sectional evaluation of hypoglossal nerve function and swallowing among OPC survivors along the cancer care continuum. The project will involve primary data collection of tongue function procedures among an active cohort (the MD Anderson Oropharynx Cohort, “MDA-OPC,” protocol #PA14–0947). Participant recruitment will occur from June 2024 to May 2026. Preliminary results of the primary objective are expected in 2027. PROs, survey responses (PSS-HN, MDASI-HN, MDADI), functional outcomes (IOPI, EIM), EMG recordings, and _HDS_EMG recordings of consenting patients will be stored on the parent cohort study (MDA #PA14–0947). Analyses herein do not overlap with the work of the parent cohort.

### Population

The population will include patients evaluated at the University of Texas MD Anderson Head and Neck Center with a suspected or confirmed pathologic diagnosis of squamous cell carcinoma (SCCA) of the oropharynx, tonsil, or base of the tongue, or of head and neck SCCA of unknown primary. Spanish-speaking participants and pregnant women may be enrolled. In this exploratory analysis, patients will be enrolled regardless of radiation dosage.

### Inclusion criteria

Patients evaluated at MD Anderson Cancer Center with pathologic diagnosis of SCCA of the oropharynx, tonsil, or base of the tongue, or SCCA of the head and neck of unknown primary who consent to EMG testing.If consented post-treatment, there is no evidence of disease

### Exclusion criteria

Primary surgery for OPC.Documented CN XII nerve injury by tumor, surgery, or other source. (Confounds radiation-induced CN XII injury.)History of prior head and neck cancer or central nervous system cancer.Functionally limiting cardiac, pulmonary, or neuromuscular disease.Current tracheostomy.History of surgery near the hypoglossal nerve path.Platelet count <50,000 cells/mL.Patient < 18 years of age.Cognitive impairment (unable to complete questionnaires).

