### Needle electromyography and nerve conduction

Intramuscular EMG will assess insertional activity in the genioglossus muscle, innervated by CN XII, as a marker of denervation [23]. Needle EMG is reported to have an inter-operator reliability of 0.53 [24]. EMG recordings will be conducted by a cancer neurologist fellowship trained in clinical neurophysiology and denervation potentials graded per standard neurologist’s grading:

0 - None

1 - Persistent, single train of potentials in at least two areas

2 - Moderate number of potentials in three or more areas

3 - Many potentials in all areas

4 - Full interference patterns of potentials

EMG and NCS may also be performed in the trapezius muscle (innvervated by CN XI), as the region is easily accessible for non-invasive testing and represents a muscle within the irradiated field with lower cranial nerve innervation. Both quantitative and qualitative EMG may be assessed [25]. Needle EMG will not be conducted if platelets are < 50,000. The intramuscular EMG will require a clinical visit with the neurologist.

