### Data management and ethics

The data collected for this study are part of a larger cohort effort to collect comprehensive outcomes data from consenting patients in the Oropharynx program at the MD Anderson Cancer Center in Houston, Texas (MDA-OPC). The collection is approved under MD Anderson IRB #PA14–0947 for MD Anderson Oropharynx Cohort patients who consent to tongue testing procedures (optional procedure #2 on the parent consent form). Patients scheduled for appointments in the Head and Neck Center will be identified by either an attending physician or an appropriately trained designee. During clinic appointments, potential subjects will be informed of their eligibility and asked if they would be interested in participating in research. In the privacy of the exam room, physicians or designees with appropriate training will discuss all aspects of the study with potential subjects and answer any questions. Subjects will be given a copy of the Informed Consent and further instructed about the study and the elements of the consent document. The subject will be given as much time as needed to review and discuss the study and consent, and the research nurse, research data coordinator, attending physician, or designee will answer any remaining questions. Non-English-speaking patients will consent to use an MD Anderson Translator and a verbal translation preparatory sheet, in accordance with MD Anderson policies for Informed Consent translation, in that patient’s primary language. Patients may withdraw from the study at any time without any penalty. The MD Anderson Institutional Review Board classifies this study as minimal risk and does not monitor this study for adverse events. The PI is responsible for monitoring adverse events. Risk will be evaluated by the electromyographer upon review of the patient’s medical history and medication.

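### The platelet exclusion limit is written per mL, which makes it 50 cells/µL and excludes practically no one before needle EMG

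*Protocol article*

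**What the plan says.** Three places in the protocol article bear on this point.

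- **Exclusion criteria.** One listed exclusion is "Platelet count <50,000 cells/mL". This is the only place where a platelet unit appears.
- **Needle electromyography and nerve conduction.** The number returns as a stop rule for the needle test: "Needle EMG will not be conducted if platelets are < 50,000". No unit is attached.
- **Data management and ethics.** A general safeguard is given: "Risk will be evaluated by the electromyographer upon review of the patient’s medical history and medication". It names no platelet value.

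The Introduction explains why a bleeding limit is needed: "needle EMG is invasive, can be performed only by trained specialists". In this study the needle enters the genioglossus from below the chin and stays in place while the patient performs the tongue tasks (High-density surface electromyography section).

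**The concern.** A platelet limit of 50,000 per mL is implausible. Taken at face value, it lies so far below any count likely to be met in a clinic that the criterion does nothing. Patients with severe thrombocytopenia would satisfy eligibility as readily as patients with normal counts.

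What is at stake is safety and the accuracy of an eligibility rule, not the statistics. No other numerical bleeding limit is given for the needle insertion. The Data management and ethics section adds that the institutional review board does not monitor the study for adverse events and leaves that to the principal investigator, which is one more reason for the written limit to be correct. The Discussion foresees multi-site follow-up work. A criterion copied from this article into such a study would carry the error to staff who did not write it.

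**Working it through.** **Inputs.** From the Exclusion criteria: limit 50,000, unit cells/mL. From the needle EMG section: limit 50,000, no unit. Conversions: 1 mL = 1,000 µL; 1 L = 1,000 mL = 1,000,000 µL.

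**The limit as written.**

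- Per µL: 50,000 / 1,000 = 50 cells/µL.
- Per L: 50,000 x 1,000 = 5 x 10^7/L = 0.05 x 10^9/L.

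**The probable intended limit** (assumption: the number is right and the unit should be µL).

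- Per mL: 50,000 x 1,000 = 50,000,000 cells/mL.
- Per L: 50,000 x 1,000,000 = 50 x 10^9/L.
- Ratio of intended to written: 50,000,000 / 50,000 = 1,000.

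**Who would be excluded.** The article gives no platelet reference range, so the counts below are assumed for illustration: three low values, and 150,000 and 400,000 as the ends of a usual range. The multiple is the count per mL divided by 50,000.

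| Assumed count per µL | Same count per mL | Multiple of written limit | Excluded as written | Excluded if per µL |
|---|---|---|---|---|
| 10,000 | 10,000,000 | 200 | no | yes |
| 20,000 | 20,000,000 | 400 | no | yes |
| 49,000 | 49,000,000 | 980 | no | yes |
| 150,000 | 150,000,000 | 3,000 | no | no |
| 400,000 | 400,000,000 | 8,000 | no | no |

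The written rule excludes none of the five. The per-µL rule excludes exactly the three low counts.

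**Does anything else in the article correct the unit?** No. The needle EMG section has the number alone, so a reader looking for its unit finds only the one in the Exclusion criteria. No section gives the limit per µL, per mm³ or in 10^9/L. The two sections do not set different limits; the second simply fails to repair the first.

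**Could a micro sign have been lost in typesetting or conversion?** This is unlikely. The High-density surface electromyography section shows the sign correctly in the amplifier noise figure (µV), and a dropped sign would normally leave cells/L, not cells/mL. A substitution of m for µ in this one place cannot be ruled out entirely.

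**The case against.** The strongest reply is that nobody would apply the limit literally. The stop rule in the needle EMG section sits at the step that creates the bleeding risk, and without a unit a clinician would read it in the customary per-µL form. The test is done by a fellowship-trained neurologist who also reviews each patient's risk. It is hard to believe that such a specialist would insert a needle at 10,000 cells/µL because of a unit in an article. On this view the point is a copy-editing slip, not a choice anyone made.

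The reply adds that the study runs under a parent cohort protocol that is not shown. The working eligibility document may carry the right unit. And no estimate, endpoint or power figure changes.

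Most of this stands as a limit on the practical effect. Literal use is improbable, the slip was almost certainly unintended, and the parent protocol may be correct. None of it makes the article's criterion right. The unitless stop rule protects patients only if the reader supplies a unit that the article never states and that differs from the one it does state. The risk review names no platelet value. A safety exclusion should not depend on the reader recognising that its unit is wrong.

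**Conclusion.** The point holds. The exclusion as written is 50 cells/µL (0.05 x 10^9/L), 1,000 times below the probable intended limit of 50,000 cells/µL (50 x 10^9/L). Applied literally, it excludes practically no one.

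The conversion is exact. Two things are assumed: that the intended unit is µL, which the investigators must confirm, and the illustrative patient counts, which the article does not supply. The conclusion is not sensitive to the counts chosen, since even the lowest is 200 times the written limit.

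The likely consequence for patients is small, and there is no material effect on sample size, power or the primary analysis. Because the error sits in an eligibility and safety threshold for an invasive procedure, it should be corrected and not left to interpretation.

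**What to change.** In the Exclusion criteria, write the limit as <50,000 cells/µL (50 x 10^9/L). In the needle EMG section, repeat the same value with the same unit. Giving both forms guards against a further unit slip. Before making the change, the investigators should confirm the intended limit against the parent protocol and, if the same error appears there, correct it as well.

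The cost is one line in each of two sections. Sample size, procedures and analysis stay as they are.

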### Objectives

#### Primary objective: Examine the feasibility of _HDS_EMG for rapid, non-invasive screening of XII nerve function.

We plan to show that a machine learning algorithm trained on features of _HDS_EMG waveforms collected during a brief series of tongue tasks will detect CN XII neuropathy and grade its severity on a continuous, more sensitive scale than existing EMG. Time-frequency features extracted from _HDS_EMG will be used to detect tongue neuropathy grade using linear discriminant analysis, ensemble machine learning classifiers, and a neural network with a multiclass activation function, providing insight into the relationship between _HDS_EMG and tongue function degradation. Tongue _HDS_EMG will also be decomposed into estimates of constituent MU spike trains for analysis with a convolutional neural network.

#### Secondary objective: Estimate the prevalence of XII neuropathy before and after oropharyngeal radiotherapy and associate it with patient-reported and clinician-graded functional outcomes.

There are no published risk estimates for CN XII neuropathy in OPC using the gold-standard electrophysiologic measurement from EMG. Existing estimates rely on clinical detection, which begins with the patient’s self-reported symptoms and proceeds to physical examination. The patient first notices the clinical manifestation of neuropathy as tongue weakness, often prompting physical examination to identify hallmark features of tongue deviation, atrophy, and fasciculation, which help diagnose CN XII neuropathy. Speech-language pathologists might also use swallow studies, speech samples, and tongue strength measures to track loss of tongue function over time. We expect needle EMG and experimental _HDS_EMG of the tongue in OPC survivors across time to reveal an increasing prevalence of CN XII neuropathy over time, as well as relationships between physiological measures and patient-perceived tongue weakening.

### Data collection

Participants consenting to the tongue testing procedures on MDA protocol #PA14–0947 will participate in measurement at baseline and/or 3–6-, 18–24-, 60-month data collection time points including: a) intramuscular EMG with or without nerve conduction study (NCS), b) tongue surface electrical impedance myography (EIM) and _HDS_EMG, c) a video recording of Lingual range of motion (L-ROM), and d) tongue strength. L-ROM and strength will be assessed using published, validated methods [21,22]. The IOPI digital manometer will measure maximum isometric lingual strength to assess maximum pressures generated by the tongue. Together, the proposed measures will characterize the nature of nerve activity, the composition of the tongue, and its function. Tongue testing procedures require a clinical appointment in the neurology center. They are expected to take about 30 minutes for EMG and up to 30 minutes, including breaks between tasks, for tongue function measures. During the visit, the study team will assign each subject an accession number that corresponds to all their deidentified data at every time point.

### Needle electromyography and nerve conduction

Intramuscular EMG will assess insertional activity in the genioglossus muscle, innervated by CN XII, as a marker of denervation [23]. Needle EMG is reported to have an inter-operator reliability of 0.53 [24]. EMG recordings will be conducted by a cancer neurologist fellowship trained in clinical neurophysiology and denervation potentials graded per standard neurologist’s grading:

0 - None

1 - Persistent, single train of potentials in at least two areas

2 - Moderate number of potentials in three or more areas

3 - Many potentials in all areas

4 - Full interference patterns of potentials

EMG and NCS may also be performed in the trapezius muscle (innvervated by CN XI), as the region is easily accessible for non-invasive testing and represents a muscle within the irradiated field with lower cranial nerve innervation. Both quantitative and qualitative EMG may be assessed [25]. Needle EMG will not be conducted if platelets are < 50,000. The intramuscular EMG will require a clinical visit with the neurologist.

### Tongue electrical impedance myography

This brief, non-invasive procedure will measure electrical conductivity in the tongue as a proxy for tongue composition. The patient’s experience is equivalent to placing a tongue depressor briefly on the tongue. The EIM system comprises a battery-powered recording unit called the user tongue electronic system (UTES) that couples to the user tongue array (UTA) depressor, custom-fabricated by [name] lab [15,16,26,27]. A smartphone is paired with the EIM system via Wi-Fi, and a custom software application allows the user to initiate the measurement, display the results, and save de-identified data.

The UTES transmits an imperceptible electrical current during a measurement through the UTA depressor. The voltage generated by the current flowing through the tongue is measured on all remaining surface electrodes. The alternating current frequency ranges from 8 kHz to 256 kHz. Across all frequencies, the current amplitude is limited to 0.1 mA, well within the safety requirements for applied current specified in the International Electrotechnical Commission (IEC) 60601−1 safety standard for medical devices. Primary EIM outcomes will include resistance, reactance, phase, conductivity, and permittivity at selected frequencies.

The UTA depressor will be for single-patient use. Each patient will have a dedicated depressor, which will be air-dried before being stored in an approved, labeled biospecimen bag between time points while not in use. The UTES will be stored with the clinical research staff when not in use and wiped with alcohol before and immediately after use. All data from the device will be automatically de-identified and sent to [name] lab for processing and analysis.

The underlying premise is that directional changes in disease tongue EIM signatures will provide new information on tongue health [16,17]. The system results from ongoing research efforts from collaborator [name] and has similar functionality and safety performance to clinical systems for impedance in other body regions. The system has been used to measure the tongue of seven healthy subjects [16]. We have conducted previous work that demonstrates the preliminary feasibility of EIM to distinguish neuropathic and healthy tongues [17]. It is approved as an investigational device for human use under IRB approval at Beth Israel Deaconess Medical Center, Boston, MA (Clinicaltrials.gov Identifier: NCT02118805). The University of Utah has submitted a provisional patent disclosure for tongue technology.

